**Methods:**

The effectiveness of the online training course will be evaluated using a cluster randomised two-arm controlled trial. Participants will be unit leaders recruited from hospitals in the Helsinki and Uusimaa Hospital District in Finland. At least 12 units will be represented, with approximately 25 participants in each unit (6 units in each arm). The sample for analysis will consist of at least 300 staff members. In the intervention arm, participants will be invited to join the online leadership course, while participants in the control group will continue practice as usual. The primary outcome is evidence-based practice, while the secondary outcomes are self-esteem, self-efficacy, implementation of EBP, quality of care, as well as work absence and intention to leave. The effectiveness of the intervention on the primary and secondary outcomes will be assessed based on the intention-to-treat principle. Feasibility data will be analysed separately. Sample size calculations are based on preliminary power analyses.

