#### Outcomes

The outcomes are targeted to evaluate the effectiveness of the evidence-based online course on an individual, team, and organisational level [4]. The primary endpoint with respect to the effectiveness of the training course is improvement in evidence-based practice (EBP) from baseline to follow-up (month 7), measured immediately after the intervention using an electronic survey administered to the unit leaders and staff.

Primary outcome.

*Evidence-based practice*: The Evidence-based Practice Questionnaire (EBPQ) [29] assesses the implementation of evidence-based practice (24 items, score 1–7, three sub-scales), focusing on [1] knowledge/skills (14 items, score 1–7, 1 = Poor–7 = Best, range 14–98, a higher score represents greater knowledge in EBP); [2] attitudes (4 items, score 1–7, range 4–28; a higher score represents a more positive attitude toward EBP); [3] evidence-based practice (6 items, score 1–7, 1 = never, 7 = frequently, range 6–42, a higher score represents more use of EBP). The instrument’s internal consistency has been rated as good, as indicated by a Cronbach’s alpha of 0.87 across the full scale [29].

Secondary outcomes.

The data for the secondary outcomes will be collected at baseline and at month 7.

*Self-esteem*: The Rosenberg Self-Esteem Scale (RSE) [30] evaluates individual self-esteem with a 10-item unidimensional scale by focusing on both positive and negative feelings about the self (4-point Likert scale, 1 = strongly agree–4 = strongly disagree). The sum score ranges 10–40, and a higher score indicates higher self-esteem. The RSE has shown high internal consistency reliability, with an average Cronbach’s alpha of 0.90 [31].

*Self-efficacy*: The General Self-Efficacy Scale (GSE) [32] assesses optimistic self-beliefs in coping with a variety of difficult life demands using 10 items (4-point Likert scale, 1 = not at all true–4 = exactly true). The sum score ranges 10–40, and a higher score indicates better coping abilities. The GSE scale has shown good reliability and unidimensionality across 25 countries, with an overall Cronbach’s alpha of 0.86 [33].

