*The implementation of EBP*: The Implementation Leadership Scale (ILS) is available in two versions, one for staff and one for supervisors [22]. The scale comprises a 12-item questionnaire measuring leadership in EBP implementation. It consists of four subscales: 1) proactive leadership, 2) knowledgeable leadership, 3) supportive leadership, and 4) perseverant leadership. It is scored from 0 (not at all) to 4 (to a very great extent), with a higher score representing stronger implementation of EBP. The ILS has demonstrated strong psychometric properties, including face, content, and construct validity as well as internal consistency and convergent validity across multiple health professional groups [34]. Internal consistency reliability has been found to be high, with a Cronbach’s alpha of 0.98 for the total scale and 0.95–0.96 for the subscales [22].

*The quality of care*: Patient death, the number of reported complaints, and medication errors will be collected from hospital records after the training course (to be balanced according to follow-up time).

*Work absence and intention to leave*: The number of days staff are absent during the course (e.g., sick leave) and intention to leave will be measured: [1] “In the last six months, how often have you planned to leave your unit”; [2] “In the last six months, how often have you planned to leave your hospital”; and [3] “In the last six months, how often have you planned to leave your profession” using a five-point scale (0 = never; 1 = now and then; 2 = quite often; 3 = very often; 4 = all the time).

After the course (month 7), course feedback will be collected (8 items developed for the study): [1] “This course was appealing to me”; [2] “I felt happy when I participated in the course”; [3] “Participation in the course required too much effort from me”; [4] “It was worth participating in this course”; [5] “I found this course valuable”; [6] “I was able to meet the requirements of the course”; [7] “This course fits well with my personal values”; and [8] “I would recommend the course to others”. Participants will consider the propositions with five possible answers (1 = completely disagree; 2 = disagree; 3 = neither agree nor disagree; 4 = agree; 5 = completely agree). Possible contamination of the study groups and any perceived adverse event or harm will be screened for during and after the intervention (months 0–7) (yes, no, not sure).

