### Sample size

A previous study indicated a 6-point increase in the EBPQ outcome from baseline to a key time point in the intervention group and a 5-point decrease over time in the control group [35]. We assume there will be a 10-point difference in the change of the primary outcome over time between the two groups and an estimated standard deviation of 20 [36]. With a power of 80%, a 5% type I error with a two-sided test, an inter-class correlation (ICC) of 0.03, and an average unit size of 25 with a variation of 1, the estimated sample at the cluster level is 12, 6 in each treatment arm. This would mean a total of 300 participants, 150 in each arm. As in many other trials, we anticipate challenges in recruitment and adherence due to the limited time and resources of nurse staff, trial-specific issues, communication difficulties, inadequate research experience and training, and a lack of incentives [37]. We assume that if 58% of participants complete the post-intervention assessment after the online training [38], the number of staff to be recruited for the study should be 517. Generally, if the average response rate for the baseline is 42% [39], we should aim to approach at least 1,238 nursing staff. The potential number of participants needed for this study is feasible, as the data will be collected in the wide region in south Finland. The power calculation was made using PASS 15 software for a cluster randomised design.

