Data analysis will be carried out on an intent-to-treat (ITT) basis; every effort will be made to collect outcome data from all participants, regardless of whether they completed the intervention. Assumptions of normality of the residuals will be investigated. The characteristics of the units and respondents (staff members) will be summarised with descriptive statistics for each group. The specific metric will be the change between the baseline score and the final score at 7 months. The method of aggregation or the summary statistics will be based on the type of outcomes. Mean score will be used for score measurement such as the EBPQ, self-esteem, self-efficacy, and EBP scales. The Quality of care and Work absence and intention to leave will be summarised using both count and proportions.

All individuals within the cluster will be included in the trial. Possible duplicate measurements will be identified using participant ID codes, email addresses, or monitoring records.

A descriptive summary of the baseline information for both clusters and individuals will be presented first as tables of summary data. For the primary outcome EBPQ, its change from the baseline to the time immediately after the intervention (key time point) will be analysed with mixed effects linear models (respondents nested within units). In such models, the mean difference in EBPQ scores from baseline to the key point of intervention will be compared between the intervention and passive control groups, with random effects among unit leaders being estimated and characteristics of participants and units being adjusted. The changes in the subscales of the EBPQ will be analysed using multivariate mixed effects models in which simultaneous models for the three subscales are analysed jointly to overcome the inter-subscale correlation that might lead to multi-comparison bias [44]. Multiple imputations for the EBPQ and its subscales will be considered if data is missing at random. The same models will be used for the secondary outcomes, such as scores on the RSE, GSE, EBP and other continuous respondent-level outcomes. For unit-level outcomes at the key point, such as death, number of reported complaints, and number of staff’s sick days, generalised linear models will be used to compare the differences between the two groups with adjustment for unit characteristics.

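### The record-based secondary outcomes are described without a pre-course count, against the protocol's own baseline statement, and with no patient or staff denominator, so estimates from 12 units may be very imprecise

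*Protocol article*

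**What the plan says.** All references are to the protocol article.

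- **Outcomes, general rule for secondary outcomes:** "The data for the secondary outcomes will be collected at baseline and at month 7".
- **Outcomes, quality of care:** deaths, complaints and "medication errors will be collected from hospital records after the training course (to be balanced according to follow-up time". No length is given for the record window.
- **Outcomes, work absence:** days absent are counted during the course. No earlier window is mentioned, and the follow-up-time clause is not attached to this outcome.
- **Data management and statistical analysis:** the general metric is the change from baseline to 7 months. Unit-level outcomes, with deaths, complaints and sick days as examples, are compared at the post-intervention time point, where "generalised linear models will be used to compare the differences between the two groups with adjustment for unit characteristics".
- **Characteristics of the units and participants:** specialty, number of beds and total staff are collected. Researchers have no access to organisational databases.
- **Eligibility:** a unit may provide specialised or primary care and needs at least 20 staff.
- **Randomisation:** stratified by unit size, split at the median staff number.
- **Number of units:** "At least 12 units will be represented" (Abstract). Under Sample size: "average unit size of 25 with a variation of 1, the estimated sample at the cluster level is 12, 6 in each treatment arm".

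**The concern.** The general statements promise a baseline and a change score for every secondary outcome. The outcome-specific statements describe a count taken after or during the course and a comparison at one time point. Both cannot hold for deaths, complaints, medication errors and absence days. The choice decides whether a pre-course extract is requested at all.

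It matters because eligible units can differ widely in patient volume and case mix. The only exposure standardisation named is follow-up time, and only for the quality-of-care counts. If all units are followed over the same seven-month course, that quantity varies little between them, whereas patient throughput and staff time can vary a great deal. Objective 4 rests wholly on these counts and objective 5 partly. Without a baseline rate or an activity denominator, their estimates depend heavily on which units fall in which arm.

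**Working it through.** **1. The number of units.** The article's figure rests on the primary outcome: "We assume there will be a 10-point difference in the change of the primary outcome over time between the two groups", "an estimated standard deviation of 20", and "With a power of 80%, a 5% type I error with a two-sided test, an inter-class correlation (ICC) of 0.03".

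- Individually randomised size per arm: 2 × [20 × (1.96 + 0.84) / 10]² = 62.8.
- Design effect with 25 per unit: 1 + 24 × 0.03 = 1.72. Then 62.8 × 1.72 = 108.0 per arm, and 108.0 / 25 = 4.32 units.
- With a t reference on 2(K − 1) degrees of freedom, power is 0.752 at K = 5 and 0.844 at K = 6. This gives 6 per arm.
- Reading the stated variation of 1 as a coefficient of variation, with a relative-efficiency correction, gives a design effect of 2.28 and 5.73 units, again 6 per arm.

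The 12 units are reproduced. The article states no precision for the record-based counts, which inherit this number.

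**2. Degrees of freedom under the stated adjustment.** With 12 units, an intercept, arm, beds, staff number and (assumed) three specialty indicators use 7, leaving 12 − 7 = 5.

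**3. Precision without a baseline.** Assumed inputs: mean count per unit μ and between-unit coefficient of variation CV.

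- Log-rate variance per unit: v = 1/μ + ln(1 + CV²).
- Standard error of the log rate ratio, 6 against 6: √(2v/6).
- 95% interval factor: exp(t × SE), with t = 2.228 on 10 degrees of freedom and no covariates.
- For CV 0.5 and μ = 50: v = 0.020 + 0.223 = 0.243, SE = 0.285, factor = exp(0.634) = 1.89.

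| CV | μ | Between-unit share of v | 95% factor | Chance of a null ratio above 1.5 or below 0.67 |
|---|---|---|---|---|
| 0.25 | 2 | 11% | 2.62 | 35% |
| 0.25 | 50 | 75% | 1.44 | 1% |
| 0.5 | 2 | 31% | 2.99 | 41% |
| 0.5 | 10 | 69% | 2.08 | 22% |
| 0.5 | 50 | 92% | 1.89 | 15% |
| 1.0 | 50 | 97% | 2.96 | 41% |

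**4. Precision with a pre-course count.** Suppose true unit rates correlate 0.7 or 0.9 over time. The correlation of the observed log rates is that value times the between-unit share of v, and the variance is multiplied by (1 − r²). For CV 0.5 and μ = 50:

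- 0.7 × 0.918 gives r = 0.64, and 59% of the variance remains (SE 0.218).
- 0.9 × 0.918 gives r = 0.83, and 32% remains (SE 0.160).
- A model with intercept, arm, size stratum and log baseline rate leaves 12 − 4 = 8 degrees of freedom (t = 2.306). The factors are 1.65 and 1.45. Without the stratum (9 degrees of freedom) they are 1.64 and 1.44.

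The gain depends on event frequency. At CV 0.5 and μ = 10 on 8 degrees of freedom the factors are 1.94 and 1.81, against 2.08 without a baseline. At μ = 2 they are 3.02 and 2.97, against 2.99, so there is no useful gain.

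**The case against.** Several points on the other side are sound.

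- **A reader might infer that follow-up time is the only standardisation.** It is not. The models adjust for unit characteristics, the relevant characteristics are collected, and randomisation is stratified by size. What stands is that no patient or staff exposure measure is named and that 12 units carry few covariates.
- **A reader might infer that no pre-course counts will exist.** The general rule for secondary outcomes says otherwise. Collection after the course may also describe when records are pulled rather than the period they cover, and the timeline figure is not shown. The supportable statement is a contradiction, clearest for absence days, which are explicitly counted during the course.
- **A reader might infer biased comparisons that mainly reflect unit type and size.** Units are randomised, so imbalance is random error, which a correctly specified interval shows. Whether unit differences dominate depends on rates that the article does not give. In similar units with rare events, chance variation in the counts dominates.
- **A reader might infer a Poisson model with inflated false positives.** In simulation, an unadjusted Poisson test at 20 events per unit and CV 0.5 rejects a true null about 42% of the time. The article names only generalised linear models, which can allow for overdispersion, and the distribution may properly be left to the analysis plan. That figure applies only if overdispersion is ignored.
- **Twelve units is a minimum.** With 25 per arm (an assumption), the factor at CV 0.5 and 50 events falls to about 1.3.

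These points limit the claim. They do not remove the conflict over timing or the value of a baseline count.

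**Conclusion.** The point holds as a contradiction to reconcile and a precision loss that is cheap to reduce. The general statements and the outcome-specific text disagree on whether the record-based outcomes have a baseline, and the named standardisation does not address patient activity or staff time.

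At the planned minimum of 12 units, CV 0.5 and 50 events per unit, the interval factor is about 1.9 without a baseline and about 1.65 to 1.45 with one. At CV 1.0 and 50 events it is 2.96 without a baseline and about 2.28 to 1.72 with one, on 8 degrees of freedom. All of this rests on assumed event rates, between-unit variation and stability over time. The benefit is clear for common events in dissimilar units and close to nil for very rare ones, which may include deaths in some units. These are secondary outcomes reported by 95% intervals only, so the trial's primary conclusion is unaffected.

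**What to change.** 1. Reconcile the general timing rule and the change metric with the outcome-specific text. State, for each record-based outcome, the window that the counts cover.
2. Request the same counts from the same records for an equal pre-randomisation window.
3. Use the log baseline rate as the main covariate beside arm and size stratum (8 residual degrees of freedom with 12 units), in place of a longer list of unit characteristics. Where counts are so low that zeros occur, state how the baseline rate enters the model.
4. Name an exposure offset: patient-days or another available activity measure for deaths, complaints and medication errors, and staff-days or staff number for absence days.
5. If a count model is used, allow for overdispersion and use a small-sample reference (t or a stratified permutation test).

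The cost is one additional retrospective extract of counts and denominators, plus revised wording. The researchers have no database access, so the organisations must be asked for the extract, and the availability of patient-days and staff-days should be confirmed first. Because the counts come from existing records, the extract remains possible although recruitment has started.

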**Fig. 1 Fig1:**
[figure not shown]
Outcomes, instruments, and specific timelines for outcome assessment using SPIRIT [15]

### Sample size

A previous study indicated a 6-point increase in the EBPQ outcome from baseline to a key time point in the intervention group and a 5-point decrease over time in the control group [35]. We assume there will be a 10-point difference in the change of the primary outcome over time between the two groups and an estimated standard deviation of 20 [36]. With a power of 80%, a 5% type I error with a two-sided test, an inter-class correlation (ICC) of 0.03, and an average unit size of 25 with a variation of 1, the estimated sample at the cluster level is 12, 6 in each treatment arm. This would mean a total of 300 participants, 150 in each arm. As in many other trials, we anticipate challenges in recruitment and adherence due to the limited time and resources of nurse staff, trial-specific issues, communication difficulties, inadequate research experience and training, and a lack of incentives [37]. We assume that if 58% of participants complete the post-intervention assessment after the online training [38], the number of staff to be recruited for the study should be 517. Generally, if the average response rate for the baseline is 42% [39], we should aim to approach at least 1,238 nursing staff. The potential number of participants needed for this study is feasible, as the data will be collected in the wide region in south Finland. The power calculation was made using PASS 15 software for a cluster randomised design.

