#### Eligibility of the clusters and individual participants

For a cluster to be eligible for participation, it should comprise a unit providing specialised or primary care with at least 20 staff members (unit leaders and other staff) and be interested in joining the study. A ‘unit’ here refers to a ward, department, or any independent operational entity that has its own immediate leader or supervisor. Units will be excluded if they have low staff capacity (fewer than 20 total staff members), if they do not provide treatment to patients (e.g., supply management, laboratory), or if they are expected to undergo significant operational changes or closures.

The online training course is designed to target unit leaders working in the social or health care sector in a managerial position. Unit leaders were selected as the primary target group of the course because they represent important first-level actors in the implementation process of evidence-based knowledge into clinical practice [22]. To be eligible for participation, unit leaders should 1) have a professional licence to work in the health or social care sector, 2) have an official managerial position at the study organisation, 3) demonstrate a willingness to join the study, 4) represent any gender, 5) be able to speak, read, and write in Finnish, 6) and give (individual level) informed consent to join the study. Unit leaders with a background in nursing or medicine (doctor, dentist) should hold positions in strategic, middle, and supervisory management within social and healthcare units [23]. Unit leaders on long-term sick leave or study leave will be excluded.

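### The response and completion rates are carried through to the headcount but not to the number of units, so the figures for units, participants per unit and staff to approach do not reconcile

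*Protocol article*

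**What the plan says.** The Sample size section of the protocol article gives these inputs: "We assume there will be a 10-point difference in the change of the primary outcome over time between the two groups", "an estimated standard deviation of 20", "With a power of 80%, a 5% type I error with a two-sided test" and "an inter-class correlation (ICC) of 0.03", with an average unit size of 25 and a variation in unit size of 1. From these it concludes that "the estimated sample at the cluster level is 12, 6 in each treatment arm", 300 participants in all. The same paragraph assumes that 58% will complete the follow-up assessment, so 517 should be recruited. With a 42% baseline response, "we should aim to approach at least 1,238 nursing staff".

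The Methods part of the abstract repeats the unit count: "At least 12 units will be represented, with approximately 25 participants in each unit (6 units in each arm". It adds that at least 300 staff will be in the sample for analysis. Under eligibility of the clusters, "it should comprise a unit providing specialised or primary care with at least 20 staff members". The Recruitment section allows expansion to new locations and departments if needed to reach the target sample size.

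**The concern.** In a cluster randomised trial, power depends on the number of clusters and the number analysed in each. Twelve units is derived for 25 analysed per unit. Once non-response and drop-out are admitted, either each unit must start with many more than 25 staff or there must be more than 12 units. The protocol says neither. It enlarges the headcount and leaves 12 units and about 25 participants per unit as they were.

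A team using the published unit count as its target could reach 12 units, each meeting the eligibility rule, and have far fewer than 300 analysed staff. The protocol gives no unit-level figure that would show this.

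**Working it through.** **Inputs.** Difference 10, SD 20, two-sided 5%, power 80%, ICC 0.03, 25 per unit, 6 units per arm, completion 0.58 and response 0.42 (all Sample size section); 20-staff minimum (eligibility section).

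**1. The plan's own figure reproduces at 25 analysed per unit.**
- Without clustering, n per arm = 2 × (1.960 + 0.842)² × 20² / 10² = 62.8.
- Design effect for equal units = 1 + (25 − 1) × 0.03 = 1.72.
- With 6 units per arm, SE = 20 × √(2 × 1.72 / 150) = 3.03. Power is 91% by normal approximation and 84% by a noncentral t test on 10 df. Five per arm gives 85% and 75%. So 6 per arm is the answer with the t test.
- If the variation of 1 is a coefficient of variation, a design effect corrected for unequal sizes is 2.28. Then 62.8 × 2.28 / 25 = 5.73, also 6 per arm, with power 82% (normal) or 73% (t). A cruder formula gives 2.47 and 6.2, so 7 per arm; 6 per arm then has 79% or 70%.

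**2. The headcount.**
- 300 / 0.58 = 517, as stated.
- 517 / 0.42 = 1,231, against the stated 1,238 (which is 520 / 0.42), a difference of 0.6%.

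**3. What the headcount implies per unit.**
- At 12 units: 517 / 12 = 43 recruited and 1,238 / 12 = 103 staff per unit.
- At 25 recruited per unit: 517 / 25 = 20.7, so about 21 units, each with 25 / 0.42 = about 60 staff.
- In units of 25 staff: 1,238 / 25 = about 50 units. In units of 20 staff: about 62 units.
- A unit at the 20-staff minimum could not supply 25 participants even with full response.

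**4. Power at 12 units.** The share of staff analysed is 0.42 × 0.58 = 0.2436. With m analysed per unit, SE = 20 × √(2 × [1 + (m − 1) × 0.03] / (6m)). Equal units; the staff counts are assumed because the protocol gives no distribution of unit sizes.

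| Scenario, 12 units | Analysed per unit | Total analysed | Power, t on 10 df | Power, normal |
|---|---|---|---|---|
| 103 staff each | 25 | about 300 | 84% | 91% |
| 84 staff each | 20.5 | 246 | 80% | 88% |
| 25 recruited each (25 × 0.58) | 14.5 | 174 | 71% | 79% |
| 25 staff each | 6.1 | 73 | 44% | 51% |
| 20 staff each | 4.9 | 58 | 37% | 44% |

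By the normal approximation, 12 equal units reach 80% at about 15 analysed each (about 61 staff).

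**5. Power if the headcount targets are met with more units (t test).**
- About 62 units of 20 staff, or about 50 units of 25 staff: 98%.
- 25 recruited per unit: 92% with 20 units, 95% with 22.

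**The case against.** The strongest reply is that the plan's own targets prevent the loss. Both rates are used, 12 is worded as a minimum, at least 300 must be analysed, at least 1,238 approached, and recruitment may be expanded. Stopping at 12 units of 20 to 25 staff would mean approaching 240 to 300 people and missing every headcount target. Meeting those targets through small units takes power well above 80%. The 20-staff figure is an eligibility minimum, not an expected size, and a unit may be a whole department.

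All of this stands, and it rules out three stronger readings. A reader might infer that the plan ignores its response and completion rates; it does not, since both enter the headcount. A reader might infer that the trial is underpowered; that follows only if recruitment stops near 12 units that are too small, which nothing in the protocol directs. A reader might also infer that 12 units suffice only with 25 analysed, or 103 staff, per unit. That is what yields 300 analysed, but with equal units 80% power is reached at about 20.5 analysed (t test) or 15 (normal).

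The reply does not reconcile the figures. The only unit count published is 12, and the provision for expansion gives no unit target or trigger.

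**Conclusion.** The concern holds as a failure to reconcile stated figures. Twelve units, about 25 participants per unit, 517 recruited and 1,238 approached cannot describe one design: 12 units need about 43 recruits and 103 staff each, and 25 recruits per unit need about 21 units. The 80% power attached to 12 units assumes that the number analysed per unit stays near 25. If 25 is the number recruited, which is a natural reading of the abstract, power at 12 units is about 71% (79% normal).

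These figures take the protocol's difference, SD, ICC and rates as given and assume equal units. If the stated variation is a coefficient of variation of 1, power is lower throughout. Actual unit sizes are unknown, so the size of any shortfall is conditional. The point should be fixed, but it does not show that the trial will miss its power. The 1,231 against 1,238 discrepancy is minor and has no effect on power.

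**What to change.** - Restate the abstract and the Sample size section so that the number of units, the recruited and analysed numbers per unit, and the headcounts agree. Two consistent examples: about 21 units (20 or 22 for equal arms) at 25 recruited each to reach about 517; or 12 units at about 43 recruited and 103 staff each.
- State that the 12-unit figure assumes about 25 analysed respondents per unit.
- Before randomisation, recompute power from the enrolled units' staff counts and baseline respondents, and report that figure if it is below 80%. The plan already collects both, and no outcome comparison by arm is needed.
- Correct 1,238 to 1,231, or 517 to 520, and say whether the unit-size variation of 1 is a standard deviation or a coefficient of variation.

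The cost is a recalculation and some rewording. The reported power may turn out less favourable; if more units are then wanted, the Recruitment section already permits expansion.
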